## Abstract

**Background:**

Sarcopenia is an age-related syndrome characterized by muscle loss and reduced muscle strength, with a high incidence rate, significantly increasing the risk of falls, fractures, and death. Baduanjin, a traditional Chinese exercise, compared with traditional rehabilitation programs, has low intensity, high safety and strong interest, and is particularly suitable for patients who cannot tolerate high-intensity exercise. This study will evaluate the therapeutic effect of Baduanjin on sarcopenia.

**Method/design:**

This trial is a multicenter randomized controlled trial that will recruit 200 participants,and is randomized (1: 1) the subjects to the intervention group (Baduanjin + health education + dietary guidance, BHD) and the control group (health education + dietary guidance, HD). After enrollment, health lectures were given to all subjects. The intervention group received 12 weeks of Baduanjin intervention, with each class lasting 70 min, once a week, and provide online guidance for home workouts four times a week, while the control group maintained their original exercise habits. Health education and dietary guidance were also provided. Observation indicators will be tested before the trial begins and during the follow-up period after the intervention ends.

**Discussion:**

This trial is a randomized controlled trial that will evaluate the intervention effect of Baduanjin on sarcopenia. According to the study of this trial, it will provide evidence for Baduanjin to improve sarcopenia.

**Clinical trial registration:**

ITMCTR2024000887.

## Background

Sarcopenia is an age-related geriatric syndrome characterized by reduced muscle mass, decreased muscle strength, reduced physical function, and decreased ability of daily living (1). The disease affects about 14 to 33% of people aged 65 and above (2). It seriously endangers the health of older adults, not only leading to a decline in their quality of life, but also increasing the risk of adverse consequences such as falls, fractures and death, causing a heavy social and economic burden (3–6).

Sarcopenia has a complex pathogenesis (7, 8). Generally speaking, it is a type of age-related disease caused by multiple factors working together. It is manifested in the reduced physical activity capacity and decreased exercise volume of older adults (1). At present, the internationally recognized treatment method is aerobic exercise, resistance exercise combined with nutritional support (9–12). However, it faces multiple restrictive factors during the implementation process,such as requirements for patients’ basic physical fitness, poor compliance with training forms, and insufficient standardization of exercise prescription implementation in primary medical institutions. Baduanjin is a traditional Chinese guiding exercise with high recognition among Chinese people. It is moderate in intensity, entertaining, safe and effective, easy to learn, and is a feasible treatment for sarcopenia (13–15). Current researches show that Baduanjin has a good effect on motor function (16–18). By combining low-intensity aerobic exercise with the transition of virtual-real gait, it simultaneously activates the core and lower limb muscle groups and strengthens proprioceptive and coordination. It can improve joint range of motion, stability and dynamic balance ability, reduce the risk of falls, and has a good effect on endurance, strength, balance and flexibility (14). In our previous clinical observation, it was found that Baduanjin enhances muscle strength in patients and improves their quality of life. In addition, Baduanjin exercises have less cardiopulmonary load and higher safety (19, 20), and are also suitable for patients with limited cardiopulmonary function or contraindications to exercise, which can effectively expand the range of people suitable for exercise rehabilitation.

However, there is currently a lack of large-sample clinical studies to verify the rehabilitation effect of Baduanjin on sarcopenia. To this end, a 20-week clinical randomized controlled trial (including a total of 12 weeks of intervention and a follow-up visit at the 20th week.) was designed to systematically evaluate the intervention effect of Baduanjin on older adult patients with sarcopenia through multiple indicators such as muscle strength, muscle mass and physical function.

## Methods

This study is designed and will be conducted and reported according to the Consolidation Standards of Reporting (CONSORT) 2010 Statement regarding randomized controlled trials (21).

### Study design

This study adopted a multicenter, randomized, controlled trial design to evaluate the rehabilitation effect of Baduanjin on sarcopenia compared with non-specific exercise (maintaining the original exercise routine without additional exercise intervention), involving a total of 200 patients diagnosed with sarcopenia. They were randomized (1:1) to the intervention group (Baduanjin + health education + dietary guidance, BHD) and the control group (health education + dietary guidance, HD), The trial procedure and outcome assessment schedule are presented in Figures 1, 2. The trial was registered on International Traditional Medicine Clinical Trial Registry on December 28, 2024 (Registration number ITMCTR2024000887).

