### Study population

#### Eligibility criteria

Diagnostic criteria (2): “Asian Working Group for sarcopenia: 2019 Consensus Update on Sarcopenia Diagnosis and Treatment” criteria for Possible sarcopenia, calf circumference (for men < 34 cm, for women < 33 cm), SARC-F scale ≥4 points, Handgrip strength (for men < 28 kg, for women <18 kg).

Inclusion criteria:

Conforming to the above diagnostic criteria;65 ≤ age ≤80;Gender is not limited;Be able to independently complete daily activities and basic communication, have no mental or neurological disorders, and be able to correctly understand the scale;The individual or co-residents are proficient in using smart devices such as smartphones;Voluntarily participate in the study and sign the informed consent.

Exclusion criteria:

Contraindications to exercise rehabilitation;Those with severe liver or kidney diseases;Patients with malignant tumors who are undergoing chemotherapy, radiotherapy or have bone metastases;Those who are unable to complete the exercise treatment program due to sprains, fractures, severe joint deformities, etc.Severe fracture osteoporosis with T value ≤ − 2.5SD and one or more brittle fractures at the same time.

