### Recruitment

The subjects of this trial will be recruited through community promotion, hospital outpatient services, etc. The subjects are from Haidian District, Beijing, China; Taiyuan City, Shanxi Province, China; Tianjin City, China; Jining City, Shandong Province, China; Suzhou City, Jiangsu Province, China. After the researchers confirm the subjects’ willingness to participate and confirm their eligibility for inclusion, the informed consent process will be carried out. After signing the informed consent form, they will be invited to participate in the trial, and the recruitment is expected to start in April 2025 and end when 200 participants are registered.

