### Baseline assessment

The researchers will collect baseline information, including participants’ general personal data and demographic information such as gender, age, history of chronic medication use, etc., and will collect all observation indicators including Handgrip strength and 30-s sit-to-stand test.

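### Entry criteria do not exclude people who already practise Baduanjin, and controls keep their usual exercise, so the treatment contrast may be diluted

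*Protocol article*

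**What the plan says.** The comparator is set out in the Study design section: the effect of Baduanjin is assessed "compared with non-specific exercise (maintaining the original exercise routine without additional exercise intervention"). The abstract, under Method/design, gives the same rule: the intervention arm receives the 12-week programme "while the control group maintained their original exercise habits". Neither place says that Baduanjin may not be part of those habits.

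The Eligibility criteria section prints both lists. Inclusion begins "Conforming to the above diagnostic criteria;65 ≤ age ≤80;Gender is not limited" and goes on to independence and communication, use of a smart device, and consent. The five exclusions begin "Contraindications to exercise rehabilitation;Those with severe liver or kidney diseases" and continue with cancer under treatment or with bone metastases, physical inability to complete the programme, and severe osteoporosis with fragility fracture. No item in either list concerns existing exercise practice.

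The Background states that "Baduanjin is a traditional Chinese guiding exercise with high recognition among Chinese people". Under Recruitment, participants will be "recruited through community promotion, hospital outpatient services, etc" in five areas of China. The Baseline assessment section gives as examples "demographic information such as gender, age, history of chronic medication use, etc", without naming exercise history. The randomisation section mentions no stratification by it, and the Statistical analysis section refers only to unspecified confounders as covariates. The Discussion concedes that participants' other activities are hard to monitor fully, but does not mention prior or continuing Baduanjin.

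**The concern.** The comparator is labelled non-specific exercise, but no rule in the article keeps the specific exercise under test out of it. A person aged 65 to 80 who meets the criteria for possible sarcopenia and already does Baduanjin regularly is eligible. In the control arm that person can carry on and still be following the plan. In the intervention arm that person moves from one form of the exercise to a more structured form of it, and may gain less than someone starting from nothing.

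Such participants contribute a reduced contrast between the arms. Randomisation spreads them evenly on average, so they do not favour either arm. The intention-to-treat effect shrinks, and with it the chance of detecting a real benefit of taking up Baduanjin. A null result would then be hard to read: it could mean that Baduanjin does little, or that too many controls were already doing it. Later covariate adjustment cannot restore a contrast that was not created, and cannot be made at all if prior practice was not recorded.

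**Working it through.** **Inputs from the Sample size calculation section.** Two-sided alpha 0.05; power 85%; 80 evaluable per group; 20% dropout; 100 recruited per group. No mean difference or SD is stated there, only a cited study of handgrip strength.

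**Input that is assumed.** The share p of entrants in each arm who already practise regularly is not in the documents. A range of 5% to 30% is used to show sensitivity. It is not an estimate.

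**The plan's own figures.** The dropout step reproduces: 80 / (1 − 0.20) = 100. The 80 per group cannot be derived forward without a difference and SD, so it is solved backwards.
- Normal formula: d = (1.960 + 1.036) × √(2/80) = 0.474.
- Noncentral t, 158 degrees of freedom: d = 0.477.

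**Worst-case dilution.** If existing practitioners gain nothing from assignment, the expected intention-to-treat effect is (1 − p) × d. Power is then taken from the noncentral t distribution with noncentrality (1 − p) × d × √(80/2). The number needed to restore 85% power is about 80 / (1 − p)² per group, then divided by 0.80 for dropout, rounding up at each step.

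| p (assumed) | Diluted d | Power at 80 per group | Evaluable per group for 85% | Total to recruit |
|---|---|---|---|---|
| 0% | 0.477 | 85.0% | 80 | 200 |
| 5% | 0.453 | 81.2% | 89 | 224 |
| 10% | 0.429 | 76.9% | 99 | 248 |
| 20% | 0.381 | 66.9% | 125 | 314 |
| 30% | 0.334 | 55.5% | 164 | 410 |

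An exact t calculation gives 163 per group and 408 in total in the last row.

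**Milder dilution.** If practitioners gain half the effect (an assumption), the effect is (1 − p/2) × d, and power is about 83% at p = 5%, 81% at 10%, 77% at 20% and 72% at 30%.

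**More favourable designs.** With 90 completers per group (10% dropout), worst-case power at p = 10% is about 82%, against 89% at p = 0. With 80 per group and baseline adjustment at an assumed correlation of 0.5, d is divided by √0.75. Power is then about 88% at p = 10% and 79% at p = 20%, against 93% at p = 0. Both assumptions raise the starting level, but the loss due to dilution remains.

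**The case against.** The strongest reply is that nothing shows the problem will occur. Wide recognition is awareness, not practice, and no prevalence is given. Entry also requires a small calf circumference, a raised SARC-F score and weak grip, which may select against regular exercisers. This stands. A reader might infer that some controls certainly receive the tested treatment, but the documents support only that they may. The 20% and 30% rows are illustrations.

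A reader might also take the control rule as an instruction to keep practising Baduanjin. The text does not go that far. It describes controls as keeping their routine with nothing added, the Control group section contains no order to continue any exercise, and the non-specific label suggests that Baduanjin was not meant to be included. Continuing is permitted, not required.

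Zero gain among practitioners in the intervention arm is a limit. The Intervention group section offers weekly supervised classes with error correction and breathing work, plus four home sessions, from which an existing practitioner could benefit. The true loss may therefore be smaller than the main table shows.

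It is tempting to add that the per-protocol analysis could not remove these people, since a control who keeps practising complies with the plan. The per-protocol set is not defined in the article, so this cannot be asserted. Likewise, the list of baseline data is open-ended, so one cannot conclude that exercise history goes unrecorded.

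Finally, adding a structured programme to usual activity is a legitimate pragmatic comparison, and the direction of any error is conservative. Both points are fair. They reduce the severity but do not close the gap, because the eligibility list and the control rule appear in the article itself and together allow the test exercise into the comparator.

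**Conclusion.** The point holds in conditional form. The printed eligibility criteria admit regular Baduanjin practitioners, and the control rule allows them to continue, so the contrast between the arms may be weaker than intended. The consequence is attenuation toward no effect and lower power. It cannot manufacture a benefit, and the randomised comparison stays valid.

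In the worst case the loss from the planned 85% is about 4 percentage points if 5% of entrants already practise, 8 if 10% do, 18 if 20% do and almost 30 if 30% do. These figures rest on an assumed p, on no contrast at all among practitioners, on an effect size solved back from 80 per group, and on an unadjusted comparison at that number. If p is near zero the issue has no practical effect. It is a cheap improvement to the design, not a flaw that invalidates it.

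**What to change.** Add to the exclusion criteria: regular practice of Baduanjin, or a closely similar traditional exercise, within a stated period before enrolment. Define what counts as regular, and establish it with one screening question at every site.

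For anyone already enrolled, add practice before randomisation to the Baseline assessment. Prespecify a sensitivity analysis of both primary outcomes (handgrip strength and the 30-second sit-to-stand test) without prior practitioners, beside the full intention-to-treat result. Classification must rest only on practice before allocation, so that the subset comparison remains randomised. Where it has to be asked after allocation, say so, because recall could differ between arms.

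The cost is a short protocol amendment, slightly slower recruitment as some interested volunteers are turned away, and results that apply to people not already practising.

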**Figure 1 fig1:**
[figure not shown]
Trial flowchart.

**Figure 2 fig2:**
[figure not shown]
Schedule of enrollment, intervention measures, and assessments.

### Sample size calculation

Revise it to read as follows:Sample size was calculated based on the inter-group independent sample mean comparison formula, the calculation is based on the research of Chang KV et al. (22) (The primary outcome measure was handgrip strength).Assuming a two-sided type I error (*α*) of 0.05 and a test power of 85% (type II error *β* = 0.15),it was calculated that 80 subjects were needed in each group (a total sample size of 160). Further considering a 20% dropout rate, ultimately 100 cases (200 cases in total) need to be recruited per group. Calculations were performed using G*Power software, version 3.1.9.7.

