#### Intervention group

BHD, guidance on the basis of health education and dietary guidance, during the intervention period, the research team will implement a 12-week standardized BDJ curriculum at fixed teaching sites (comprising one 70-min centralized session weekly). The course will adopt a four-module framework: biomechanical analysis of BDJ movements, consolidation and error correction of acquired techniques, new movement instruction, and group practical guidance. Dietary education and health guidance will be systematically integrated throughout the intervention process. After completing nine BDJ foundational training (including preparatory postures), participants will advance to movement trajectory optimization and respiratory rhythm regulation phases, designed to enhance movement precision. Subjects will perform standardized home-based training using instructional videos, completing daily 30-min BDJ practice sessions (4 times/week), combined with centralized sessions to achieve a weekly training frequency of 5 sessions (1 centralized + 4 home-based). A dual-time-point video documentation protocol (pre- and post-intervention) will be employed to archive visual records for instructional standardization control and movement quality evaluation.

During the trial, no necessary routine medical treatment was ruled out for either group of subjects. If drugs such as growth estrogen and testosterone were used to improve sarcopenia, they should be reported to the researchers, and the researchers should record the medication situation of the subjects in a timely manner.

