### Statistical analysis

Data will be analyzed by independent statisticians using the SPSS 27.0 software package. The primary analysis will adhere to the intention-to-treat (ITT) principle, supplemented by per-protocol (PPS) analysis, with a two-sided *p < 0.05* defined as statistical significance. Missing data will be addressed using multiple imputation methods. Continuous variables will be described as mean ± standard deviation (SD) or median (interquartile range, IQR), and categorical variables as frequencies (percentages). Baseline characteristics between the intervention group and the control group will be compared using *independent-samples t*-tests (for normally distributed data) or *Mann–Whitney U* tests (for non-normally distributed data). Categorical variables will be analyzed using chi-square tests or Fisher’s exact tests. Primary and secondary outcomes will be evaluated using mixed-effects linear models with restricted maximum likelihood (REML). The models will include group (Baduanjin/control), time (baseline/post-intervention), and other potential confounding factors as covariates.

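### The sample size makes no allowance for class clustering in the intervention arm and the listed model terms name no class or centre, so power falls short of 85% if classmates' outcomes are correlated

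*Protocol article*

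**What the plan says.** Under Sample size calculation, the protocol article states: "Sample size was calculated based on the inter-group independent sample mean comparison formula". The named outcome is handgrip strength, with two-sided alpha 0.05 and 85% power. This gives 80 analysed per arm. The only inflation follows: "Further considering a 20% dropout rate, ultimately 100 cases (200 cases in total) need to be recruited per group". No effect size, standard deviation, design effect, class size or ICC is given.

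Under Intervention group, the delivery is described: "the research team will implement a 12-week standardized BDJ curriculum at fixed teaching sites". There is one 70-minute session a week, and group practice is one of the four course modules. Four further 30-minute sessions a week are done at home from videos. Randomization is by individual participant, 1:1, and Recruitment lists five localities.

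Under Statistical analysis, the outcomes are to be analysed by mixed-effects linear models fitted by REML: "The models will include group (Baduanjin/control), time (baseline/post-intervention), and other potential confounding factors as covariates". The random effects are not described.

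**The concern.** Participants are randomized individually, but those in the intervention arm are then taught together for 12 weeks. People in one class may come to resemble each other through the teaching, the site, attendance habits or the group itself. Controls have no Baduanjin class. This is a partially nested design, in which an effective sample of 80 per arm is reached only if the within-class ICC is zero.

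Two things are at stake. The first is planning: any positive ICC takes power below 85% at the planned size. The second is inference: an analysis that leaves class out would understate the standard error of the treatment effect, so that confidence intervals are too narrow and the test rejects too often. The first follows from the stated formula once the ICC is positive. The second also requires that class is absent from the final model.

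**Working it through.** **Inputs from the protocol article.** Two-sided alpha 0.05, power 85%, 80 analysed per arm, 20% dropout (Sample size calculation); five localities (Recruitment); weekly classes in the intervention arm (Intervention group).

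**Assumptions, because the article gives no figures.** Within-class ICC of 0.01, 0.02 or 0.05. Either five classes with m = 16 analysed (one per locality, 80/5), or ten classes with m = 8 analysed. Clustering in the intervention arm only, with the same total SD in both arms.

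**Step 1: the plan's own figure.** The 80 per arm cannot be derived afresh without an effect size. Solving backwards, the normal approximation gives d = (1.960 + 1.036) × √(2/80) = 0.474, and the t-test gives 0.477. For comparison, d = 0.45 needs 89–90 per arm and d = 0.50 needs 72–73. The dropout step reproduces: 80/(1 − 0.20) = 100.

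**Step 2: variance under one-arm clustering.** The design effect in the intervention arm is DE = 1 + (m − 1) × ICC. In SD units, Var(difference) = DE/80 + 1/80, so the variance is inflated by (1 + DE)/2 relative to independence. For m = 16 and ICC 0.05: DE = 1 + 15 × 0.05 = 1.75, inflation = 2.75/2 = 1.375, and the SE ratio is √1.375 = 1.173.

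**Step 3: type I error if class is ignored.** This is 2 × Φ(−1.96/√inflation). For the same case, 2 × Φ(−1.96/1.173) = 9.5%.

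**Step 4: power when class is modelled.** With k classes, the Satterthwaite degrees of freedom are df = (v₁ + v₂)² / [v₁²/(k − 1) + v₂²/79], where v₁ = DE/80 and v₂ = 1/80. Power comes from the noncentral t with noncentrality 0.477/√(v₁ + v₂). For the same case, df = 9.7, the critical value is 2.237, the noncentrality is 0.477/0.1854 = 2.57, and power is 64%.

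**Step 5: interval width.** The ratio to the interval that ignores class is the SE ratio × t(df)/t(158), with t(158) = 1.975. At one end (m = 8, ICC 0.01) it is 1.017 × 2.040/1.975 = 1.05. At the other (m = 16, ICC 0.05) it is 1.173 × 2.237/1.975 = 1.33.

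| Classes | ICC | DE | SE ratio | Type I error if class ignored | df | Power, Satterthwaite |
|---|---|---|---|---|---|---|
| 10 of 8 | 0.01 | 1.07 | 1.017 | 5.4% | 30.6 | 82% |
| 10 of 8 | 0.02 | 1.14 | 1.034 | 5.8% | 29.2 | 80% |
| 10 of 8 | 0.05 | 1.35 | 1.084 | 7.1% | 25.7 | 76% |
| 5 of 16 | 0.01 | 1.15 | 1.037 | 5.9% | 13.5 | 77% |
| 5 of 16 | 0.02 | 1.30 | 1.072 | 6.8% | 12.2 | 73% |
| 5 of 16 | 0.05 | 1.75 | 1.173 | 9.5% | 9.7 | 64% |

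A normal approximation with d = 0.477 gives 84%, 83% and 79% for m = 8, and 83%, 80% and 73% for m = 16. Those figures count the extra variance but not the cost of estimating it from few classes. They should not be quoted alongside an analysis that uses small-sample degrees of freedom.

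**The case against.** A reader might infer that the planned model treats everyone as independent and that its confidence intervals are therefore too narrow. The article does not show this. It names a mixed-effects model without describing the random effects, leaves the covariate list open, and is a condensed account whose analysis plan is not at hand. A class or centre effect is not excluded. This objection stands, and it makes the standard-error and type I error statements conditional on class being omitted. It does not touch the sample size, which is stated in full with an independence formula.

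A reader might also take a loss of power as established. It is not, since class size, number of classes and ICC are all missing. Some features of the delivery may keep the ICC low: the curriculum is standardized, home practice follows videos, and 120 of the 190 weekly training minutes (4 × 30 out of 70 + 120) are at home. With ten small classes and ICC 0.01, the extra variance alone costs only about one point of power. This stands as a reason to show a range, but nothing in the article rules out the larger losses.

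Finally, the control arm might not be free of clustering. The abstract mentions lectures for all subjects, and controls receive structured education. Whether this is given in groups is not stated, so one-arm clustering is the plausible reading and not a certain one.

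**Conclusion.** The point holds in conditional form. The stated 85% power assumes a within-class ICC of zero, which does not fit easily with the shared classes that the article describes. For assumed ICCs of 0.01 to 0.05, power under an analysis that models class is about 76–82% with ten classes of 8 and 64–77% with five classes of 16. If class is left out of the final model, the type I error is about 5.4–7.1% and 5.9–9.5% respectively. All of this rests on the assumed ICC and class sizes, on an effect size back-solved from the 80 per arm, and on clustering in the intervention arm only. The documents do not support a flat statement that the trial is underpowered or that its intervals will be wrong.

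**What to change.** - **Data collection:** record a class ID for every intervention participant, and an education-group ID for controls if their education is given in groups. This has to be done during delivery, because a class that was never recorded cannot be modelled later.
- **Statistical analysis:** name centre as a fixed effect and class as a random effect in the intervention arm (and education group in the control arm, if it applies), with Satterthwaite or similar small-sample degrees of freedom.
- **Sample size calculation:** state the expected class size, number of classes and an assumed ICC, and restate power at the planned 200 participants on the same basis as the analysis.

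The cost is one CRF field, additional model terms and a less favourable power figure, with no extra participants. Confidence intervals would be about 5–33% wider than those that ignore class, depending on the number of classes and the ICC. One limit should be stated openly: with a single class per centre, class variation cannot be separated from treatment-by-centre variation, and its estimate rests on five units.

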### Randomization, assignment of hiding and blinding

The randomization sequence will be generated using computer-generated random numbers, and participants will be allocated to either the intervention or control group in a 1:1 ratio. Allocation concealment will be ensured by an independent third party utilizing opaque, sealed, sequentially numbered envelopes. The randomization operation was carried out by the staff of the GCP Center of Xiyuan Hospital of China Academy of Chinese Medical Sciences. Although blinding is difficult to implement in this trial, data analysts and result evaluators will follow the blinding principles when processing the data. In addition, objective measures were chosen as the primary outcome measures in this trial to minimize measurement bias.

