#### Primary outcome measures

##### Handgrip strength test and 30-s sit-to-stand test

Handgrip strength test (23) is a commonly used functional assessment method in clinical practice. It measures the maximum force produced by isometric contractions of the flexor muscle groups in the forearm of the subject with a standardized handheld dynamometer, and the test results objectively reflect the functional status of the upper limb skeletal muscles and neuromuscular coordination.

30-s sit-to-stand test (24) is a standardized test for assessing lower limb functional ability, requiring subjects to complete as many sit-to-stereoscopic position changes as possible within 30 s without upper limb assistance, reflecting quadriceps muscle strength, hip flexor coordination and dynamic balance ability through counting, and is widely used in geriatric functional assessment and sports injury rehabilitation monitoring.

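### Two primary outcomes are named, but the trial is sized on handgrip strength alone at an undivided 0.05, with no success rule or testing order in the article

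*Protocol article*

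**What the plan says.** Four places in the Protocol article bear on this.

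- **Primary outcome measures** puts two tests under one subheading, "Handgrip strength test and 30-s sit-to-stand test", and does not rank them.
- **Randomization, assignment of hiding and blinding** also uses the plural: "objective measures were chosen as the primary outcome measures in this trial".
- **Sample size calculation** uses one outcome. After citing an earlier study as its basis, it adds in parentheses "The primary outcome measure was handgrip strength". The error rate is not divided ("Assuming a two-sided type I error (*α*) of 0.05") and the power is 85%. The result is 80 per group, raised to 100 per group (200 in total) for 20% dropout. No mean difference, standard deviation or standardised effect is given.
- **Statistical analysis** sets one threshold, "with a two-sided *p < 0.05* defined as statistical significance", and one class of model for everything: "Primary and secondary outcomes will be evaluated using mixed-effects linear models".

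The article does not say whether success means one primary outcome or both, or which is tested first. It gives no power for the sit-to-stand test.

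**The concern.** The stated 5% error and 85% power describe a trial with one primary test. The outcome section describes a trial with two. The two descriptions agree only under certain decision rules, and the article states none.

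The gap affects the trial's main claim. With the rule open, the investigators could report success on whichever primary outcome crosses 0.05, and a reader could not tell whether that was planned. If the rule is instead that both must cross, the chance of success is lower than the sample size section implies. The choice has to be made before outcome data are seen, because a rule chosen afterwards would not be credible.

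**Working it through.** **Inputs from the Protocol article.** Two-sided alpha 0.05, power 85%, 80 evaluable per group, 20% dropout (Sample size calculation); 1:1 allocation; two primary outcomes (Primary outcome measures).

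**Assumptions, because the article gives no figure.** The correlation ρ between the two test statistics is varied from 0 to 0.9. Sit-to-stand is given the same 85% power as handgrip.

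**Step 1: the plan's own figures.** The dropout step reproduces: 80 / (1 − 0.20) = 100 per group, 200 in total. The 80 cannot be reproduced because no effect size is stated, so the effect is solved for instead:

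d = (z₀.₉₇₅ + z₀.₈₅) × √(2/80) = (1.960 + 1.036) × 0.1581 = 0.474.

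With the noncentral t distribution, d is 0.477. The rest uses this implied effect.

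**Step 2: success on either outcome, each tested at 0.05 without adjustment.** For independent tests the family-wise error is 1 − (1 − 0.05)² = 1 − 0.9025 = 9.75%. With correlation it is 1 − P(|Z₁| < 1.960 and |Z₂| < 1.960) under a bivariate normal. It cannot exceed 0.05 + 0.05 = 10%.

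**Step 3: both must succeed, each at 0.05.** For independent tests joint power is 0.85 × 0.85 = 72.25%. With correlation it is P(Z₁ < 1.036 and Z₂ < 1.036).

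| ρ | Error, either counts | Power, both needed |
|---|---|---|
| 0 | 9.75% | 72% |
| 0.3 | 9.5% | 74% |
| 0.5 | 9.1% | 76% |
| 0.7 | 8.3% | 78% |
| 0.9 | 7.0% | 81% |

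The error exceeds 5% in every row, and joint power is below 85% in every row. To bring joint power to 85% would take about 102 evaluable per group at ρ = 0, or 95 at ρ = 0.7. After dropout that is 128 or 119 per group.

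**Step 4: alpha split equally (Bonferroni, 0.025 each) at 80 per group.** The critical value is 2.241 and the expected test statistic is 1.960 + 1.036 = 2.996. Power per outcome is Φ(2.996 − 2.241) = Φ(0.755) = 77.5% (77.3% with the t distribution). Restoring 85% per outcome takes 96 per group, or 96 / 0.8 = 120 per group after dropout (240 in total).

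**Step 5: Holm at 80 per group.** Handgrip is significant if it passes 0.025, or if it passes 0.05 and sit-to-stand passes 0.025. At ρ = 0 its power is 0.775 + (0.850 − 0.775) × 0.775 = 0.833. At ρ = 0.7 the bivariate normal gives 0.818. Handgrip therefore has about 82% to 83% power. The chance that at least one outcome succeeds, under Holm or Bonferroni, is about 87% (ρ = 0.7) to 95% (ρ = 0).

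**Step 6: fixed sequence, handgrip first.** Handgrip is tested at the full 0.05, so its 85% power stands. Sit-to-stand is tested only after handgrip succeeds, so the family-wise error stays at 5%. The sample size does not change.

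**The case against.** Four arguments deserve weight.

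*A testing rule is the sort of detail an article leaves to the full protocol or analysis plan.* This is fair, and the missing rule alone would not be a finding. But the number of primary outcomes and the alpha and power behind the sample size are stated here, and they do not match. An analysis plan that split alpha or required both outcomes would change what the published 85% means. One that let either count without adjustment would exceed 5%.

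*The article never commits to testing each outcome at an unadjusted 0.05 with either one sufficient.* This is correct. A reader might infer that rule from the single threshold and conclude that the trial has a 9% to 10% error rate. The text does not support that. A general threshold is compatible with adjusted p-values, a testing order or a requirement that both succeed. Also, 9% to 10% holds only for correlations up to about 0.5.

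*The parenthesis about handgrip may describe the cited study.* It follows the citation directly and is in the past tense, so the reading is possible. A reader might take it as a flat statement that this trial has one primary outcome, and the wording does not settle that. On either reading, handgrip is the only outcome used for sizing while two are listed as primary.

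*Inflated error and lost power are not the only possibilities.* This also stands. A fixed sequence starting with handgrip, or one named primary outcome, avoids both. The article states neither.

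**Conclusion.** The point holds as a mismatch in the stated text: two primary outcomes, and a sample size built for one at an undivided 0.05. Its consequences depend on the rule eventually adopted:

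- either counts, unadjusted: error about 8% to 10% for correlation 0.7 to 0, and 7% at 0.9;
- both needed: power about 72% to 78% for correlation 0 to 0.7, and 81% at 0.9;
- equal alpha split: about 77% power per outcome;
- fixed sequence with handgrip first: no loss for handgrip.

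The error figures rest only on the assumed correlation. The joint power, Holm and at-least-one figures also rest on the assumed 85% power for sit-to-stand. The alpha-split and Holm figures take the published 80 per group and 85% power at face value, through an effect of about 0.474 to 0.477 that is back-solved and not stated. Other assumptions would change the size of the problem but would not remove the mismatch.

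**What to change.** **Preferred.** Name handgrip strength as the single primary outcome in the outcome, blinding and analysis sections, to match the sample size. Make the 30-s sit-to-stand test the first key secondary outcome, tested at two-sided 0.05 only if handgrip is significant at 0.05. This needs wording changes only. The cost is that sit-to-stand cannot carry a confirmatory claim if handgrip fails.

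**If both are to stay primary.** State the success rule and restate the power to match it. At 80 evaluable per group, quote about 77% per outcome for Bonferroni, or about 82% to 83% for handgrip under Holm (correlation 0.7 to 0). The 77% figure should not be used for Holm, because it understates handgrip's power. If both must succeed, quote 72% to 78% or enlarge the trial. In each case, give the planning effect for both outcomes and the assumed correlation.

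In the sample size section, also say whether the handgrip parenthesis refers to this trial or to the cited study. Make the change before any outcome data are examined by group.
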